## Abstract

**Introduction::**

Extralevator abdominoperineal excision (ELAPE) may cause various surgical complications including disruption of perineal wound, perineal hernia and adhesive small-bowel obstruction. Pelvic peritoneum reconstruction (PPR) could prevent those complications, but it may not always be achievable, especially in patients with severe pelvic fibrosis after neoadjuvant radiotherapy. Our previous study has reported the application of the PPR using the bladder peritoneum flap in laparoscopic ELAPE. The aim of the study is to evaluate the short-term clinical, technical and safety outcomes of PPR using the bladder peritoneum flap in laparoscopic ELAPE.

**Methods and analysis::**

This is a multi-center prospective single-arm cohort study and fulfill the IDEAL 2A stage principle. Rectal cancer patients undergoing laparoscopic ELAPE, suffering rigid pelvis or huge perineal peritoneum defect, and having difficulty in primary perineal wound closure will be considered eligible. Main exclusion criteria are being complicated with urgent complications, ASA grade >3 and accompanied with mental illness. After informed consent, 30 patients are planned to be included in the study. Standard laparoscopic ELAPE with pelvic peritoneal floor reconstruction using bladder peritoneum flap are to be performed. The surgical safety is to be evaluated after one-year follow-up. Primary endpoints are the occurrence of intraoperative and postoperative complications of PPR using the bladder peritoneum flap. Second endpoints are overall complication rate within 30 days after surgery, extent of small intestine falling down to pelvic cavity, and other follow-up consequences within 1 year after surgery.

**Ethics and dissemination::**

This experiment was approved by the Biomedical Ethics Committee of West China Hospital of Sichuan University.

**Trial registration::**

NCT04177407.

## Introduction

1

In rectal cancers, the overall survival will benefit strongly if a negative circumferential margin is reached. In order to pursue a negative margin, the extralevator abdominoperineal excision (ELAPE), which was introduced by Holm et al^[1]^ have been used to improve the oncological outcome in T3 and T4 low rectal cancer.^[2]^ However, after removal of the rectum and mesorectum, ELAPE leaves a dead pelvic space, which may allow the intraabdominal contents to descend. When the small bowel protrudes into the dead space and adhere to the pelvis, the risk for intestinal obstruction rises.^[3]^ In addition, the descending small bowel may further herniate through the perineal wound, leading to perineal hernia (PH). The downward pressure of intraabdominal content may also compromise the healing of perineal wound.^[4]^

Pelvic peritoneum closure with running suture is a partition technique, which is believed to be capable of separating the abdominal and pelvic cavity, thus prevent the small bowel from descending into the pelvic dead space. Studies have demonstrated that pelvic peritoneum closure could reduce the incidence of perineal wound complications, intestinal obstruction and PH.^[5]^ However, pelvic peritoneum reconstruction (PPR) may not always be feasible, especially in patients who had received a neoadjuvant radiotherapy and suffered severe tissue fibrosis in the pelvis (a rigid pelvis) or those who have no redundant peritoneum coverage and conventional closure may under high tension.^[2,5]^

Recently we have reported a novel method, using the bladder peritoneum flap to reconstruct the pelvic peritoneum in laparoscopic ELAPE for 3 patients with a rigid pelvis after neoadjuvant radiotherapy.^[2]^ According to the IDEAL framework, which describes a pathway for testing surgical innovation, the previous technical note belongs to IDEAL stage 1 as it described proof of concept. In order to further develop the bladder peritoneum flap closure procedure, we intend to conduct an IDEAL stage 2a prospective development study.

## Methods

2

### Study objectives

2.1

The objective of this study is to evaluate the short-term clinical, technical and safety outcomes of PPR using the bladder peritoneum flap in laparoscopic ELAPE.

### Study design

2.2

This is a multi-center, prospective development study. The method of PPR using the bladder peritoneum flap in laparoscopic ELAPE is at the development stage. And this protocol fulfills the requirement of IDEAL framework stage 2A.^[6]^

Approval of the ethics committee has been obtained from the ethics committee of West China Hospital, Sichuan University (2019 No. 194). The present study was registered on the clinicaltrials.gov (NCT04177407) on November 27, 2019. For adopters from other institution, approval of the local ethic committee will be required. Procedure development with reasons for changes will be presented to the institutional review board for further assessment. Benefits and risks of the study will be informed to participants. Only participants who signed an informed consent form and agree to participate will be included in this study. Participants have the right to quit the study at any time without any reason. In emergency circumstances, surgeons have the right to end the study. Data of the details will be stored in a database and published after the trial.

### Study endpoints

2.3

The primary endpoints are the occurrence of intraoperative and postoperative complications of PPR using the bladder peritoneum flap in laparoscopic ELAPE.

Intraoperative complications include bleeding, flap devitalization, flap laceration, bladder injury and any other event that may cause the failure of the novel method. Postoperative complications include complicated perineal wound healing, PH, presacral sinus and small-bowel obstruction (SBO) within 1 year after surgery. Perineal wound healing is evaluated using the Southampton wound score system, and a score ≥ IV is regarded as complicated perineal wound healing.^[7]^ PH was defined as the presence of intra-abdominal content beyond a line connecting the coccyx and the lower margin of the pubic symphysis on sagittal views of CT.^[8]^ PH will be further classified as symptomatic and asymptomatic PH, regarding to patient's complaint of symptoms and physical signs. Presacral sinus is defined as accumulation of fluids in the presacral dead space after removal of rectum and mesorectum. SBO is classified according to the Clavien-Dindo classification^[9]^ and reasons for obstruction will be recorded (adhesive, tumor metastatic or stoma-related).

Secondary end points include:

(1)Overall complication rate within 30 days after surgery.(2)The incidence of the presence of the small bowel in the retro-urogenital space, which was define as space between the bladder/uterus and the sacrum on axial views of CT.(3)1-year overall survival and tumor free survival.(4)Quality of life at baseline, 3 months, 6 months, and 12 months after surgery.(5)Bladder and prostatic function evaluation at baseline, 3 months, 6 months, and 12 months after surgery.

### Population

2.4

Consecutive patients with primary or recurrent rectal cancer eligible for laparoscopic ELAPE will be included in this study. If a patient has a rigid pelvis after neoadjuvant chemoradiotherapy and the peritoneum reconstruction could not be done by a running suture, the patients will be considered as a candidate for the bladder peritoneum flap closure. A rigid pelvis is defined as a stiff pelvis with no redundant peritoneal coverage because of severe fibrosis caused by neoadjuvant radiotherapy. In addition, if PPR with a running suture is with high tension, the patient will also be included to receive the bladder peritoneum flap closure. All patients with PPR will be also included as comparison. Details of the inclusion and exclusion are formulated in the Table 1.

**Table 1 T1:**
[figure not shown]
Details of the inclusion, exclusion criteria.

Usually, in a Stage 2A study, a single institution with some early adopters is involved for technique-based innovations. However, our study requires that the adopter should have sufficient experience of laparoscopic ELAPE (30 or more cases experience) and routinely perform PPR. In our center, only 1 other colorectal surgeon fit this requirement. Therefore, we will invite surgeons from other institution who meet the requirement to join us and make the present study a multicenter study.

### Operative procedures

2.5

All the laparoscopic ELAPE should follow the principle of total mesorectal excision and the perineal part of ELAPE procedure should follow the principles proposed by Holm et al. Video of surgery should be saved for further check.

After transection of the rectum, if PPR with running suturing is not feasible, the bladder peritoneum flap closure is performed. The procedure of the bladder peritoneum flap closure was described in the previous stage 1 study,^[2]^ briefly, it has 3 main steps:

(1)Flap planning. In the laparoscopic view, the bladder peritoneal flap has an arch shape or “U” shape with the bottom at the anterior wall of the pelvic cavity entrance. The height of the arched flap is equal to the distance from the bladder to the sacral promontory. We measured the distance with a 15-cm suture, and then determined the highest point of the flap and marked it with electrocautery.(2)Flap harvest. The electrocautery was set at a low power level and used in a cutting mode. The peritoneum was incised at the planned level and peeled off the bladder. Sharp dividing in close proximity to the muscular layer of the bladder, combined with blunt separation, was applied to maintain a good blood supply to the flap.(3)Flap suturing. Rotate the harvest flap to cover the entrance of the pelvic cavity. The closure is then completed with a running suture (Prolene, Ethicon Inc, Cincinnati, OH) from the right side to the left, by suturing the free edge of the flap to the brim of the pelvis (Fig. 1).

**Figure 1 F1:**
[figure not shown]
The pelvic peritoneum was reconstructed using the bladder peritoneum flap.

Evolving of procedure. In the development study, 2 more steps are to add to the procedure. First, to reduce potential abdominal adhesion introduced by the rough surface of bladder and the flap, an anti-adhesion barrier (INTERCEED, Ethicon Inc, Cincinnati, OH) is then used to cover the rough surface of the bladder and the flap. Second, to determine the flap's vitality, after flap harvest, a near-infrared fluorescent dye (indocyanine green fluorescence [ICG]) is injected to the rotated flap and an imaging system is used to detect blood supply of the flap. If vascular perfusion via ICG is poor or delayed, the flap closure is considered as a failure.

For patients who are feasible for PPR with conventional running suturing, they will be still included as comparison.

### Collection and analyses of data

2.6

Surgery related data collection. Surgical videos of all the included patients will be evaluated by the major center (Department of Gastrointestinal Surgery, West China Hospital of Sichuan University). Intraoperative information of primary tumor, operation time, data related to pelvic peritoneal reconstruction, postoperative recovery and postoperative pathology will be collected. Intraoperative complications are evaluated by operators during the surgery.

Follow-up data collection. Follow-ups will be performed by professional officers via outpatient service, phone or letter. The follow-up period is set as 1 year. Life quality is evaluated by EORTC QLQ-C30, EORTC QLQ-CR29 quality of life scale. Prostatic function is evaluated by international prostatic symptom score and bladder function is appraised by bladder residual urine. Schedule of follow-ups is listed in Table 2. Laboratory tests performed in none- research centers are accepted in the follow-up. However, radiological examination should be performed in the research centers.

**Table 2 T2:**
[figure not shown]
Follow up items and time.

### Statistics

2.7

The hypothesis of our study is to test superiority of the bladder peritoneum flap closure over no closure in patients who are not eligible for PPR. The currently available literature of PPR is difficult to interpret with regard to complicated perineal wound healing, PH and SBO. Owing to lack of high-quality data in the literature, we define a clinically relevant difference in complicated perineal wound healing, PH and SBO which could justify the use of the bladder peritoneum flap closure. The difference is considered to be 30%. A total of 30 patients in the study group are needed to be able to detect a 30% reduction in the incidence of 1-year complicated perineal wound healing, PH and SBO by performing the bladder peritoneum flap closure from 45% to 15% (α = 0.05, 1-β = 0.80, superiority margin = 0.05, dropout rate = 0.1).

As stated in the part of Population, there will not be a control group. The study will be stopped if complication rate shows much higher (over 10%) than that the comparison group. Outcomes are reported in “Study endpoints” section.

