## Discussion

4

This multi-center, prospective development study is an IDEAL framework stage 2a study. Through this stage of study, we hope to:

(1)modify the bladder peritoneum flap closure to minimize potential risks of complications;(2)make the procedure refine enough at the end of stage 2a study to allow replication in later IDEAL stage study;(3)evaluate if this procedure could be adopted by other surgeons successfully;(4)evaluate the short-term clinical, technical and safety outcomes of the bladder peritoneum flap closure.

To prevent the small bowel or intraabdominal content from entering the pelvic dead space, several surgical methods have been adopted but there is no consensus on what the best method is. Generally, these methods can be divided into 2 categories: partition techniques and filling techniques. Partition techniques separate the abdominal and pelvic cavity with closed pelvic peritoneum^[5,10]^ or prosthesis.^[11]^ Filling techniques are to fill the pelvic dead space with a pedicled omentoplasty,^[12]^ myofascial flap or breast prosthesis.^[13]^ The omentoplasty seems to be the most popular technique, especially in laparoscopic ELAPE, in which suturing of pelvic peritoneum is sometimes technically demanding.^[5,10]^ However, a recent meta-analysis demonstrated that the omentoplasty is associated with increased risk for PH and perineal wound complications because non-vital omentoplasty may cause pelvic infection and subsequent complications.^[12,14]^ Traditionally, pelvic peritoneum is primarily closed after ELAPE by a running suture, barbed suture or Hem-o-lok clips.^[5,10]^ In some scenarios, reconstruction of pelvic peritoneum is difficult because of high tension. Modifications could be made to reduce the tension, such as making a shallow incision on both sides of the surface of pelvic peritoneum.^[5]^ Nevertheless, if there is no redundant pelvic peritoneum coverage, especially when the patient has a rigid pelvis after neoadjuvant radiation, either conventional or modified pelvic peritoneum closure is not feasible. Under these circumstances, even surgeons who routinely perform PPR may choose not to close the pelvic peritoneum. Currently, to our knowledge, there is no other studies on PPR regarding these situations. Our novel technique using the bladder peritoneum flap to reconstruct pelvic peritoneum in laparoscopic ELAPE could offer a new option to colorectal surgeons.

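### The stated hypothesis, superiority over no closure, cannot be tested because no unclosed comparison group is observed; the 30 patients fit a one-sample test against an assumed 45%

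*Protocol article*

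**What the plan says.** Statistics (2.7) gives the hypothesis as "to test superiority of the bladder peritoneum flap closure over no closure in patients who are not eligible for PPR". It sizes the study group at 30 patients to detect a fall from 45% to 15% in the 1-year incidence of complicated perineal wound healing, perineal hernia (PH) and small-bowel obstruction (SBO). The stated inputs are alpha 0.05, power 0.80, superiority margin 0.05 and dropout 0.1.

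On the origin of the difference it says: "Owing to lack of high-quality data in the literature, we define a clinically relevant difference". The Discussion adds, about patients in whom neither conventional nor modified closure is feasible: "Currently, to our knowledge, there is no other studies on PPR regarding these situations".

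On the design, the Abstract says "This is a multi-center prospective single-arm cohort study", and Statistics says "As stated in the part of Population, there will not be a control group". Population (2.4), to which that sentence refers, says "All patients with PPR will be also included as comparison". Operative procedures (2.5) says "For patients who are feasible for PPR with conventional running suturing, they will be still included as comparison". The stopping rule in Statistics also refers to a comparison group.

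**The concern.** The hypothesis names two treatments in one population: flap closure and no closure, both in patients who cannot have conventional pelvic peritoneum reconstruction (PPR). Only the first is observed. The comparison patients differ from the missing group in treatment, because they are closed, and in population, because a running suture was feasible for them.

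The 45% therefore stands in for the whole missing group, and it has no data behind it. If the true no-closure rate is lower, a flap that changes nothing could be reported as superior, and the nominal alpha would not describe the error rate of the claim as worded. At stake is how a favourable flap rate is presented: as meeting a fixed goal, or as a demonstrated benefit over leaving the peritoneum open.

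**Working it through.** **Inputs.** All are from Statistics (2.7): reference rate 0.45, target rate 0.15, margin 0.05, alpha 0.05 (sidedness not stated), power 0.80, dropout 0.10, study group 30.

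**1. Reproducing the 30.** One-sample proportion with superiority margin, two-sided alpha, null variance at 45%:

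n = [1.96·√(0.45·0.55) + 0.8416·√(0.15·0.85)]² / (0.45 − 0.15 − 0.05)² = (0.9751 + 0.3005)² / 0.25² = 1.627 / 0.0625 = 26.03, so 27. Then 27 / 0.9 = 30, which matches.

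The exact match depends on the variance choice and on sidedness. With the null variance at the 40% boundary, (0.9602 + 0.3005)² / 0.0625 = 25.43, so 26, and 26 / 0.9 = 28.9, so 29. One-sided versions give 23 to 28 after dropout.

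**2. The same inputs as a two-group comparison.** Unpooled variance, two-sided:

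n per group = (1.96 + 0.8416)²·(0.2475 + 0.1275) / 0.25² = 47.09, so 48; 48 / 0.9 = 53.3, so 54 per group.

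Across one- and two-sided versions and variance choices, the result is 43 to 58 per group after dropout. A two-group formula comes near 30 only if the margin is dropped and alpha is one-sided (29 or 32 per group), or if the margin is applied with the opposite sign (28 or 30 per group). Either would need a second group of the same size. The one-sample reading is thus the best reconstruction, but it is an inference.

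**3. Who is observed.**

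| Patients | Peritoneum closed? | Eligible for running-suture PPR? | Role in the plan |
|---|---|---|---|
| Flap patients | Yes, by flap | No, or only under high tension | Study group, 30 |
| Running-suture patients | Yes | Yes | Comparison |
| Flap failures on fluorescence imaging (Discussion) | No | No | Counted as failures of the study procedure |
| Ineligible patients managed without closure | No | No | None enrolled; no external cohort named |

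The last row is the comparator in the hypothesis.

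**4. What a positive one-sample result shows.** With the margin, the boundary is 0.45 − 0.05 = 0.40. Assume that the three outcomes form one any-event composite and that alpha is one-sided 0.025. The exact rule takes the largest c with P(X ≤ c | n, 0.40) ≤ 0.025, and power is P(X ≤ c | n, 0.15):

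| Evaluable n | Success if events ≤ | Size at 40% | Power at 15% |
|---|---|---|---|
| 27 | 5 | 0.015 | 79% |
| 28 | 5 | 0.011 | 76% |
| 29 | 6 | 0.023 | 87% |
| 30 | 6 | 0.017 | 85% |

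**5. Dependence on the 45%.** Suppose the flap has no effect, so that its rate equals the true no-closure rate p. The documents give no value for p, so the range is assumed. P(X ≤ 5 | 27, p) is:

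| p | Probability of meeting the rule |
|---|---|
| 35% | 5% |
| 30% | 14% |
| 25% | 30% |
| 20% | 54% |

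**6. Precision.** With 4 events in 27 (14.8%), close to the target rate, the exact 95% confidence interval is 4.2% to 33.7%. Such a result would support a benefit only if the no-closure rate were above about 34%.

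**The case against.** The strongest reply is that a single arm is ordinary at IDEAL stage 2a and is openly declared. The article says that there is no control group, assigns the 30 to the study group, and admits that high-quality data are lacking and that the authors set the difference themselves. Superiority over no closure appears in one sentence. Study objectives (2.1), the four aims in the Discussion and the closing paragraph are descriptive; the last offers the flap as a possible option that still needs proof. All of this stands. It limits the harm, and it means that no control arm is being asked for. It does not remove the conflict, because the same sentence introduces the sample size, and no passage supplies an unclosed group or a source for the 45%.

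Two further replies also stand in part. Sidedness and the test are not stated, so the one-sample match is a reconstruction. The article never says that the three outcomes form a composite, so the success rule above is conditional on that.

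A reader might go further and infer that the sample size is wrong, that the study is an underpowered two-group trial, or that its planned conclusions fall as a whole. The documents do not support this. The 30 reproduces as a one-sample size, the text rules out a two-group design, and no superiority conclusion is written into the objective or aims.

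**Conclusion.** The point holds as a mismatch between hypothesis and design. Superiority over no closure in PPR-ineligible patients cannot be tested with the patients described. What can be tested is whether the 1-year rate after flap closure is below 40%, a goal derived from an assumed 45% less the 5-point margin.

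The sample size is not in error: 30 is reproduced, given two-sided alpha and null variance at 45%. The 14% and 30% probabilities are illustrations at assumed no-closure rates of 30% and 25%; they are not error rates taken from the plan. They show that the nominal alpha protects the claim against a fixed goal, not the claim as worded. The descriptive objective, aims and endpoints are unaffected.

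**What to change.** Keep 30 patients and change the wording of Statistics (2.7):

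- Restate the hypothesis as: the 1-year rate after flap closure is below a fixed goal of 40% (45% less the 5-point margin), with the 45% labelled as an assumption.
- Remove superiority over no closure from the hypothesis and from any conclusion.
- State whether complicated perineal wound healing, PH and SBO form one any-event composite, and that alpha is two-sided 0.05 (one-sided 0.025).
- If both are confirmed, give the exact success rule: at most 5 events of 27, 5 of 28, 6 of 29 or 6 of 30 evaluable.
- Report the exact 95% confidence interval, and read its upper limit as the lowest no-closure rate for which a benefit would be supported. Readers can then judge the result without relying on the 45%.
- Reconcile the statement that there is no control group with the comparison patients in Population and Operative procedures and the comparison group in the stopping rule. Say what those patients are used for.

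The cost is protocol wording and a weaker claim. The 40% goal still rests on an unsourced figure, which is why the interval should be reported beside the test.

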PPR is a well-accepted procedure to prevent perineal wound complications and intestinal obstruction in open abdominoperineal resection (APR).^[15]^ Despite this, there are only few evidences of application of PPR in laparoscopic APR/ELAPE. Yan et al recently reported that patients with PPR has a lower rate of perineal surgical site infection, delayed perineal healing, ileus and PH compared to patients without pelvic perineum reconstruction.^[5]^ To be noticed, in their study, the rate of PH was 0% in patients with pelvic perineum reconstruction, but it was based on data during the hospitalization. Similarly, Xu et al^[16]^ used Hem-o-lok clips to reconstruct pelvic peritoneum in laparoscopic APR for 22 patients with low rectal cancer or anorectal cancer, and there was no PH after 3 months. In the study of Wang et al,^[10]^ they compared the outcomes between patients with PPR along with primary perineal wound closure and patients with biological mesh closure for perineal wound without PPR. Their results showed that PPR was associated with shorter postoperative hospital stay and lower cost. The 1-year surgical outcomes were comparable between PPR with primary closure and biological mesh closure and there was no 1-year PH. In our previous study reporting 33 cases of laparoscopic ELAPE with PPR, there was also no symptomatic PH after 12 months follow-up and only 1 intestinal obstruction (3.0%, 1/33). Therefore, based on evidences from literatures and our own experience, we routinely perform PPR in laparoscopic ELAPE.

In the previous stage 1 study,^[2]^ we reported 3 cases using the bladder peritoneum flap to reconstruct pelvic peritoneum in patients with a rigid pelvis undergoing laparoscopic ELAPE In the past 9 months, we performed another 3 bladder peritoneum flap closure for patients with a rigid pelvis. Patient selection was extremely strict as we only perform this procedure in patients after neoadjuvant radiotherapy. As mentioned above, fibrosis in the pelvis is not the only condition for the failure of conventional PPR. In obesity patients or patients with bulky tumor, the pelvic perineum coverage may also be insufficient.^[5]^ Therefore, to accelerate the inclusion of patients, we would expand our inclusion criteria and not limit to patients with neoadjuvant radiation.

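### The stopping rule benchmarks flap patients against running-suture patients, who are easier to close by selection and are not the comparator of the hypothesis, so a flap meeting its 15% target could well trigger it

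*Protocol article*

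**What the plan says.** **The rule (2.7 Statistics).** "The study will be stopped if complication rate shows much higher (over 10%) than that the comparison group". The article does not say which complication rate is meant or whether 10% is an absolute or a relative excess.

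**The group it refers to.** The sentence just before the rule reads "As stated in the part of Population, there will not be a control group". Section 2.4 (Population) does not say that. It says "All patients with PPR will be also included as comparison". The end of 2.5 (Operative procedures) narrows this: "For patients who are feasible for PPR with conventional running suturing, they will be still included as comparison". The Abstract calls the study single-arm.

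**Who gets the flap (2.5).** "if PPR with running suturing is not feasible, the bladder peritoneum flap closure is performed". Section 2.4 gives the reasons: a rigid pelvis after neoadjuvant treatment, or a running suture under high tension.

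**The comparator of the hypothesis (2.7).** The aim is to test "superiority of the bladder peritoneum flap closure over no closure in patients who are not eligible for PPR". The sample size assumes a fall in 1-year complicated perineal wound healing, perineal hernia (PH) and small-bowel obstruction (SBO) "by performing the bladder peritoneum flap closure from 45% to 15" per cent.

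**What is known about running-suture patients (4 Discussion).** In the authors' own series of 33 cases, "there was also no symptomatic PH after 12 months follow-up and only 1 intestinal obstruction (3.0%, 1/33").

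**The concern.** The two groups are split by the anatomical difficulty that motivates the study. A patient is in the comparison group because ordinary closure worked, and in the flap group because it did not. A higher complication rate with the flap is what such selection would tend to produce, whether or not the flap does harm.

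The question the trial asks is whether the flap beats leaving the peritoneum open in patients who cannot be closed conventionally. The rule does not look at that. A flap that cut the rate from 45% to 15% would be a success by the hypothesis, and could still be stopped because patients who never needed a flap did better.

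The primary endpoint in 2.3 adds a further asymmetry. It counts flap devitalization and flap laceration, which cannot occur without a flap. If the rule's rate includes them, they can only push it towards stopping.

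At stake is a development study ended, or continued, on a contrast that does not measure harm from the procedure.

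**Working it through.** **1. Does the design need a concurrent group?** Inputs from 2.7: p0 = 0.45, p1 = 0.15, margin 0.05, α = 0.05 (taken as two-sided), power 0.80, dropout 0.1. A one-sample test against a fixed p0 gives

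n = [z(0.975)·√(p0(1−p0)) + z(0.80)·√(p1(1−p1))]² / (p0 − p1 − margin)²
= (0.975 + 0.301)² / 0.25² = 26.03, rounded up to 27; 27 / 0.9 = 30.

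This reproduces the stated 30. On this reading the sample size rests on a fixed 45% reference and needs no concurrent patients. Only the stopping rule uses the running-suture group.

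**2. The expected gap.** With the flap at 15%, a gap of more than 10 points is expected when the running-suture rate is below 15 − 10 = 5%. At 3% the gap is 12 points; at 10% it is 5.

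**3. Probability that an on-target flap triggers the rule.** Assumptions, because the article leaves them open: the rate is the 1-year composite, 10% is absolute, there is one look at the end, and the comparison group has 27 to 90 patients with true rate pc. Then

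P(stop) = Σ over x, y of Bin(x; nf, 0.15)·Bin(y; nc, pc), summed where x/nf − y/nc > 0.10.

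Hand check for nf = nc = 30 and pc = 0.03. With 0, 1, 2 or 3 comparison events, the flap group needs at least 4, 5, 6 or 7 events. The probabilities of those comparison counts are 0.401, 0.372, 0.167 and 0.048. The probabilities of the flap counts are 0.678, 0.476, 0.289 and 0.153. The sum is 0.272 + 0.177 + 0.048 + 0.007, plus about 0.001 for higher counts, which is 0.505.

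| Running-suture rate | 30 v 30 | 30 v 60 | 30 v 90 | 27 v 27 |
|---|---|---|---|---|
| 3% | 50.5% | 54.8% | 56.5% | 63.1% |
| 5% | 40.5% | 43.7% | 44.9% | 52.8% |
| 8% | 28.0% | 29.4% | 29.8% | 39.1% |
| 10% | 21.4% | 21.7% | 21.7% | 31.4% |
| 15% (no difference) | 10.1% | 9.0% | 8.5% | 16.8% |

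The 27 v 27 column gives every upper end. One reason is discreteness: 3/27 is 11.1% and over the limit, while 3/30 is exactly 10% and not over it.

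**4. The relative reading.** If the rule means a flap rate more than 1.1 times the comparison rate, P(stop) with 30 v 30 is 93% at 3%, 87% at 5%, 65% at 10% and 43% at equal rates.

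**5. Which row applies?** The 3.0% in the Discussion is 1/33 for SBO alone. The PH result there covers symptomatic hernia only, whereas 2.3 counts hernia defined on CT and includes asymptomatic cases. No wound-healing rate is given for that series. The running-suture composite is therefore not in the article, and 3% is an assumption at the favourable end.

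**The case against.** The strongest reply has four parts.

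*The comparison group is real.* A reader might infer that 2.7 relies on a group it says does not exist. The text does not support that. It denies a control group, not the comparison group, and 2.4 and 2.5 plainly enrol the latter. Since the hypothesis is flap versus no closure, the sentence can be read as saying there is no no-closure arm. What stands is that the cross-reference to Population is wrong, and that the terms in the Abstract, 2.4, 2.5 and 2.7 do not fit together.

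*The 15% and the 3% are different endpoints.* This is correct. Setting a three-part composite against obstruction alone does not show that an on-target flap breaches the limit. At a running-suture rate of 8-10% the single-look probability is about 21-39%.

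*The rate may be another one.* Section 2.3 also has an overall 30-day complication rate. If the rule means that, neither 15% nor 3% applies. The selection problem remains, but the figures above do not carry over.

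*Repeated looks and late read-out are assumed.* Looks after 10, 20 and 30 flap patients with equal comparison numbers would raise P(stop) to about 63% at 3%, 37% at 10% and 24% at equal rates, but the article states no such schedule. A reader might also infer that 1-year events arrive too late to protect anyone. With 30 patients in 13 months, the tenth reaches one year at 10/(30/13) + 12 = 16.3 months, after all operations. With accrual below 20/12 = 1.67 a month, the tenth reaches one year before the thirtieth operation. The lead centre reports 3 flap cases in 9 months. Nor is the rule the only safeguard: 2.2 lets surgeons end the study in emergencies, and 2.8 provides safety monitoring, patient withdrawal and ethics-committee reporting.

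None of this changes who is being compared with whom. The benchmark is stated in the article; it is not a detail left to a fuller document.

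**Conclusion.** The concern holds as a wrong benchmark. The only numerical study-level stopping rule compares flap patients with patients selected for easier closure, who are not the comparator of the hypothesis and cannot have flap-specific complications. A flap at its own 15% target could well trigger it: about 51-63% if the running-suture rate is 3%, 41-53% at 5%, 21-31% at 10% and 9-17% at equal rates. These figures assume the 1-year composite, an absolute 10 points, one final look, 27-30 flap patients and 27-90 comparison patients.

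The stronger statement, that a successful flap would probably stop the trial, is not established. On the absolute reading with one look it needs a running-suture composite rate of about 5% or less, and the article gives no such rate. On the relative reading it would hold up to a rate of about 10%, but nothing in the text selects that reading.

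**What to change.** 1. **Reconcile the text.** Make the Abstract, 2.4, 2.5 and 2.7 agree: there is no concurrent no-closure control group, and running-suture patients are enrolled as a descriptive comparison. Correct the cross-reference to Population.
2. **Remove the running-suture group as the stopping benchmark.**
3. **Base the study-level rule on the flap group alone.** Name the event set and its time window, state the looks, and set a fixed limit. The sponsor chooses the limit and justifies it for that same event set and window. The 45% is a 1-year no-closure composite and should not be carried over to intraoperative or 30-day events.
4. **Report the operating characteristics.** Give the probability of stopping at the target rate, at the limit and above it, for the stated looks.

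The cost is protocol wording and a short operating-characteristics table. No extra patients are needed.
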